We aim to conduct a double-blind randomized controlled trial including a nonrandomized, reference BG to assess the efficacy of a ready-to-feed, liquid, bovine milk–based whey, predominant term infant formula containing 2-fucosyllactose and lacto-N-neotetraose from the first 2 weeks of age up to age 6 months in Chinese infants. We will also study its effects postintervention for up to age 12 months in promoting appropriate gut maturation and supporting immune functions. The primary objective of this trial is to show an increase in *Bifidobacteria* abundance in the experimental group (EG, which will receive ready-to-feed infant formula containing 2 HMOs) compared to the control group (CG, which will receive the same ready-to-feed infant formula without the 2 HMOs) at age 3 months. Secondary objectives include comparing the following outcomes among all the feeding groups (EG, CG, and BG): fecal microbiome and metabolic profile, fecal markers of immune health, gut barrier integrity, and inflammation, gastrointestinal tolerance, adverse events (AEs), infant immune competence, infant sleep quality, infant growth, and infant quality of life from enrollment up to age 12 months.

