### Randomization Procedure and Blinding

Participants will be assigned to the EG or CG groups randomly using Medidata Randomization Trial Supply Management with the dynamic allocation algorithm at the first visit. An allocation ratio of 1:1 stratified by site, sex (female or male), and mode of delivery (cesarean section [CS] or vaginal) will be carried out. Neither the investigator or site team nor the participant will know which investigational product each participant is receiving until after database lock. Considering the double-blinded nature of the trial, the identity of the specific product will be blinded to participants, participants’ parents, or caregivers (if applicable), support staff, investigators, site team, contract research organization managing the trial (except specified delegated regulatory staff), and study sponsors (except the manufacturing site, supply, and quality managers). The products will be identical in packaging, color, and taste. They will be packaged and labeled identically but will have distinguishable product codes printed on the packaging. Unblinding will be done only in case of emergency or after database lock for final statistical analyses.

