### Data Analysis

#### Sample Size

The sample size was calculated based on the primary end point of the trial and an additional nonrandomized breastfed arm. To demonstrate a statistically significant increase of 8% in relative *Bifidobacteria* abundance at 3 months in the EG versus CG infants with a power of 80% and an α-level of 5%, a sample size of 105 per arm (including a 20% attrition rate) will be needed. For the nonrandomized breastfed reference arm, assuming a noninferiority margin of 20% in *Bifidobacteria* abundance with the experimental formula arm, the required sample size will be 52 infants (including a 20% dropout rate). Therefore, the total sample needed for this trial will be 262 infants (105 EG, 105 CG, and 52 BG).

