For all categorical and continuous variables, appropriate descriptive statistics will be calculated by visit, feeding groups, and delivery mode. The primary end point of the difference in *Bifidobacteria* abundance between EG and CG infants will be analyzed using analysis of covariance (ANCOVA), correcting for baseline, site, gender, and mode of delivery. If the investigation of data reveals an inflation of the null values (no detected *Bifidobacteria* in samples), then the ANCOVA model will be replaced by a 0-inflated mixture model. For continuous secondary end points, ANCOVA models correcting for baseline, site, gender, and delivery will be used for analyses. For categorical secondary end points, logistic regression models will be used to compare between feeding groups at each time point separately. Fecal metabolism and immune health markers will be analyzed according to dry stool weight, using an ANCOVA model at each time point to compare between feeding groups, correcting for baseline, site, gender, and mode of delivery. The necessity to log-transform the end points or to use nonparametric methods will be assessed during the blind data review and addressed in the statistical analysis plan. During the final analysis, the models may be modified to a mixed model repeated measurements to consider the longitudinal nature of the data. AEs will be compared between feeding groups using the Fisher exact test.

Missing data will be assumed to be missing at random unless the blind review of the data demonstrates a pattern of missingness, in which case, multiple imputation for the primary outcome of *Bifidobacteria* abundance at 3 months may be used. In the case of outliers for any end point, robust approaches or sensitivity analyses may be used. Statistical testing for all end points will be 2-sided and at a 5% significance level. All statistical analyses will be performed in SAS Life Science Analytics Framework (version 5.4.1; SAS Institute Inc).

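### The fecal-marker ANCOVA reads as one model across EG, CG and the nonrandomized BG, so the standard error of the randomized EG-CG contrast can be wrong if BG variability differs

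*Protocol article*

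**What the plan says.** All references are to the protocol article.

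- **Primary end point** (Statistical Analysis): the contrast is between the two randomized arms. "The primary end point of the difference in *Bifidobacteria* abundance between EG and CG infants will be analyzed using analysis of covariance (ANCOVA"), adjusted for baseline, site, gender and mode of delivery.
- **Fecal metabolism and immune markers** (same section): these are analyzed on dry stool weight "using an ANCOVA model at each time point to compare between feeding groups, correcting for baseline, site, gender, and mode of delivery".
- **Other continuous secondary end points**: "For continuous secondary end points, ANCOVA models correcting for baseline, site, gender, and delivery will be used for analyses". This sentence names no groups.
- **Categorical secondary end points**: "For categorical secondary end points, logistic regression models will be used to compare between feeding groups at each time point separately". Adverse events are compared by the Fisher exact test.
- **Which groups are meant** (Introduction): the secondary objectives are described as "comparing the following outcomes among all the feeding groups (EG, CG, and BG").
- **Status of BG**: randomization covers the formula-fed infants only, "An allocation ratio of 1:1 stratified by site, sex (female or male), and mode of delivery". Sample Size and the Discussion both describe BG as a nonrandomized reference.

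The same section leaves log transformation and nonparametric methods to the statistical analysis plan. It also allows a later change to a mixed model for repeated measures. The model type, the covariates and the comparison across feeding groups are stated in the article itself.

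**The concern.** The wording changes from EG and CG for the primary model to feeding groups for the fecal markers, and the Introduction gives that term three members. Read together, these passages point to a single ANCOVA with EG, CG and BG as levels of one factor.

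A default ANCOVA has one residual variance for all its rows. BG infants would then help to set the standard error of the EG-CG contrast, although they carry no direct information on EG versus CG. They are self-selected and have a different feeding history. Under the eligibility criteria they have been exclusively breastfed since birth, while formula infants need only three days of exclusive formula before enrollment. There is no design reason to expect equal residual spread.

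EG versus CG is the only randomized comparison for these markers, and each is tested at two-sided 5%. Its validity should not depend on how variable a nonrandomized reference group happens to be.

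**Working it through.** **Step 1. Evaluable numbers (Sample Size).** The randomized arms give 105 × 0.8 = 84 each. BG gives 52 × 0.8 = 41.6, about 42. The planned total reproduces: 105 + 105 + 52 = 262. The 8-point effect with 80% power, two-sided 5% and 84 per arm implies an SD of about 18.5. The article does not state this SD, and it concerns the primary end point. No SD is given for any secondary end point in any group, so the relative variability of BG has to be assumed.

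**Step 2. Weight of BG in the error variance.** Ignoring the few degrees of freedom spent on covariates, BG's share is 42 / (84 + 84 + 42) = 42 / 210 = 0.20.

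**Step 3. Effect on the EG-CG standard error.** Let k be the BG SD divided by the formula-arm SD. The pooled variance relative to the formula-arm variance is (168 + 42k²) / 210 = 0.8 + 0.2k². The reported standard error is therefore multiplied by f = √(0.8 + 0.2k²). Then:

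- Type I error = 2 × [1 − Φ(1.96 f)]
- Power, for an effect that has 80% power with the correct standard error = 1 − Φ(1.96 f − 2.80)

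| k (assumed) | f | Type I error | Power |
|---|---|---|---|
| 0.5 | √0.85 = 0.92 | 7.1% | 84% |
| 0.71 (variance ratio 0.5) | √0.90 = 0.95 | 6.3% | 83% |
| 1 | 1.00 | 5.0% | 80% |
| 1.41 (variance ratio 2) | √1.20 = 1.10 | 3.2% | 74% |
| 2 | √1.60 = 1.26 | 1.3% | 63% |

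The power above 80% in the first two rows comes with the inflated type I error and is not a gain.

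**Step 4. Simulation check.** There were 20,000 runs per scenario with 84/84/42 infants and a baseline slope of 0.5 in the formula arms. With the same slope in BG, the three-group model with common variance and slope rejected a true null in 7.0%, 6.2%, 5.0%, 3.2% and 1.5% of runs for the five rows above. This agrees closely with the formula. A model on EG and CG only gave 4.9% to 5.3% in every scenario.

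**Step 5. Bias and baseline slope.** The mean EG-CG estimate under a true null stayed within about 0.002 SD units of zero throughout. With equal variances, a BG slope of 0 instead of 0.5 gave type I error 4.9%, and a reversed slope of −0.5 gave 3.9%. The slope is a minor matter beside the variance.

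**Step 6. Cost of leaving BG out when variances are equal.** Count an intercept, the group terms, baseline, four site terms, sex and delivery mode. The two-arm model keeps 168 − 9 = 159 residual degrees of freedom and the three-arm model 210 − 10 = 200. The two-sided 5% critical values are about 1.975 and 1.972, so the loss is negligible.

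**The case against.** The strongest reply is that the article never states the pooled model. Comparing between feeding groups may name the comparisons without saying which rows enter the model. The same phrase is used for adverse events, where the Fisher test has no residual variance. Separate pairwise ANCOVAs, or one model with group-specific variances, would also fit the text, and such detail often sits in the statistical analysis plan, which is not shown. This stands in part. The three-group model is the natural reading, not a quoted specification. But the article does fix the model type and the groups compared, does not list them among the items it defers, and nowhere confines the secondary EG-CG contrast to the randomized infants.

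A second reply is that unequal variance is unproven. That is correct. The Discussion expects *Bifidobacteria* to be depleted in formula-fed infants, which concerns level, not residual spread after adjustment. Log transformation, nonparametric methods or robust approaches, all of which the article allows, might also narrow a difference in spread.

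A reader might infer that the secondary error bars are simply wrong, or that every secondary end point is affected. The documents support neither. At equal variance and slope the test is correct. The quoted sentence covers the fecal markers, and the other continuous end points come in only by implication of the Introduction. Logistic models and the Fisher test have no pooled residual variance. The Pediatric Immune System Index and the quality-of-life questionnaire have no first-visit value in Table 1, so they have no baseline slope of their own.

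**Conclusion.** The point holds as a conditional weakness with a cheap remedy. It applies directly to the fecal metabolism and immune markers and, by implication, to the other continuous secondary end points. It rests on two assumptions: that EG, CG and BG enter one ANCOVA, and that the model keeps the default common residual variance.

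Its size depends on a BG-to-formula SD ratio that the article does not give. Across ratios from 0.5 to 2, the EG-CG standard error runs from about 8% too small to about 26% too large. Type I error runs from about 7% down to about 1%, and at a ratio of 2 power is about 63% instead of 80%. At a ratio of 1 there is no error. The direction cannot be settled from the document.

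The EG-CG estimate is not biased by this, and the primary end point, described as EG versus CG only, is not affected.

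**What to change.** State that EG-CG contrasts for continuous secondary end points are estimated from a model containing only the two randomized arms, as for the primary end point. If the mixed model for repeated measures is adopted, the same restriction should apply. State that EG-BG and CG-BG contrasts come from a separate model with group-specific residual variances and are labeled nonrandomized.

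This should be settled before the first staged analysis, at the 3-month visit, because the article treats staged estimates as final.

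The cost is a sentence or two in the analysis plan and one extra model run per end point. It needs no additional infants or data, and precision is almost unchanged if the variances prove equal (step 6 of the working).

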#### Compliance With Investigational Product

Compliance with feeding interventions will be monitored throughout the trial using various tools, such as a formula milk intake diary and breastfeeding questionnaire at specified visits. Data on nontrial feeding will also be recorded at specific time points to inquire about regimen interruptions and consumption of unauthorized feedings or supplements. Each trial day in which trial formula intake or exclusive breastmilk feedings are interrupted will be counted as a noncompliant day. Throughout the trial, noncompliance will be calculated based on formula-fed infants being off trial formula or breastfed infants being off breast milk and consumption of prebiotics or probiotic-containing supplements, with some minor modifications based on specific visits.

The number of noncompliant and compliant days will be determined, and a compliance rate as a percentage of compliant days concerning total potential days of exclusive feeding (approximately 100 days, but individual for each infant, depending on the enrollment age) will be calculated for each participant and dropout participant. Participants with a compliance rate of less than 80% will be considered as having a major protocol deviation and will not be included in the PPS. All noncompliance between V2 and V5 will be considered minor protocol deviations.

#### Trial Discontinuation

Discontinuation from the trial product may happen for the following reasons: parents or LARs withdraw consent to participate, or the investigator decides to discontinue the trial if they opine that continued exposure to the trial product would be detrimental to the participant’s well-being. No additional data will be collected, and no further analyses will be performed if consent is withdrawn. The reason for premature discontinuation will be documented, and the investigator will follow up regarding any unresolved AEs.

### Data Management, Monitoring, and Dissemination

#### Data Management

Site personnel will manually enter source data (clinical findings and observations, laboratory and test data, questionnaires, site notebooks, and paper diaries) into the electronic Case Report Form (eCRF) web database, which is 21 CFR Part 11 compliant. The clinical data manager will review and validate all entered data. The eCRF database will be locked after cleaning of the data, which includes review, query resolution, signatures by the investigators, and determination that the database is ready for analysis. All documents on the conduct of the study will be kept by the investigator for 5 years after the study’s completion.

#### Data Monitoring

The monitoring plan will be developed and agreed upon between the sponsor and the contract research organization responsible for the monitoring at the site on the monitoring activities to be compliant with the protocol, Good Clinical Practice Guidelines, local regulations, and the sponsor’s procedures, and to ensure the subjects’ well-being and data integrity. At agreed-upon times during the trial and after the trial has been completed, the investigator will allow sponsor representatives to periodically review the eCRF and corresponding records (source documents) of each trial participant. These monitoring visits will allow the sponsor or sponsor representative to examine trial progress, verify completeness and accuracy of eCRF, resolve any inconsistencies in the records, and ensure that all protocol requirements and obligations are being fulfilled. The sponsor representatives or external auditors will be permitted by the investigator to conduct an audit of the trial during the trial or after the trial ends. This will be to ensure compliance with the Good Clinical Practice Guidelines, local regulations, the trial protocol, and the sponsor’s procedures, as well as evaluating the accuracy of the trial data.

Regular data quality reviews are organized to identify any data inconsistencies. To ensure data quality, automatic edit checks that identify inconsistencies have been set up and flagged as queries during the data entry process. For more complex data where these automated checks cannot be implemented, manual review will be performed.

### Ethical Considerations

Ethics approvals were granted by all the independent ethics committees of all the hospitals joining in the study, which are the Ethics Committee of Xinhua Hospital Affiliated to Shanghai Jiao Tong University School of Medicine (XHEC-C-2024-024-2), the Ethics Committee of Shanghai First Maternal and Infant Hospital (2024 027), the Ethics Committee of The International Peace Maternity and Child Health Hospital of China Welfare Institute (GKLW-A-2024-024-02), the Ethics Committee of the Peking University Third Hospital (2024 878-02), and the Ethics Committee of Nanjing Women and Children’s Healthcare Hospital (2024FYYL007). All parents or LARs will sign an informed consent form (see example in Additional File S2 in Multimedia Appendix 1). In the event of a screen failure, that is, consent was signed but the participant was not subsequently enrolled, information related to the reason for screen failures will be documented.

This study will be conducted per the ethical principles outlined in the Declaration of Helsinki and in compliance with all applicable regulatory requirements, including China’s Clinical Trial laws, the Personal Information Protection Law, and the Measures for Science and Technology Ethics Reviews (effective as of December 2023).

All participants will receive comprehensive written and verbal information about this study’s objectives, procedures, potential risks, and benefits. Written informed consent will be obtained from each participant before any study-related procedures.

To ensure the protection of participants’ rights, safety, and well-being:

AEs will be monitored and managed per regulatory and ethical standards.Personal and health data will be collected, stored, and processed in full compliance with Personal Information Protection Law requirements.Participants will be informed of their right to withdraw from the study at any time without penalty.

Special attention will be given to the recruitment of breastfeeding mothers. Per the WHO International Code of Marketing of Breast-Milk Substitutes, no coercive or promotional practices were used. Participation will be entirely voluntary, and all information will be provided neutrally and respectfully to ensure informed and independent decision-making.

The study will be conducted by qualified investigators and supported by institutional quality assurance processes to ensure ethical conduct and regulatory compliance throughout. The study has been registered on ClinicalTrials.gov (NCT06361719), and results will be submitted to a peer-reviewed journal for dissemination; the role of authors and contributors will be defined according to International Committee of Medical Journal Editors guidelines. The study will be carried out according to the SPIRIT (Standard Protocol Items: Recommendations for Interventional Trials) guidelines. The completed SPIRIT checklist is provided in Additional File S3 in Multimedia Appendix 1.

Every precaution will be taken to protect the privacy of research participants and the confidentiality of their personal information. The investigator will ensure protection of the participant’s personal data and of all reports, publications, participant samples, and any other disclosures, except where required by law. Participants are identified only by a participant identification number and site identification number to maintain participant confidentiality. All participant study records will be kept safely in an access-controlled area. Identification code lists linking participant names to participant identification numbers will be stored separately from participant records. In case of data transfer, the sponsor will maintain high standards of confidentiality and protection of participant personal data. Clinical personal information will not be released without the written permission of the participant, except for monitoring by regulatory authorities or the study sponsor. The investigator or designee will comply with all applicable data protection laws and implement and maintain appropriate technical and organizational measures against the unauthorized or unlawful acquisition, access to, or processing of Personal Data and against the accidental loss, disclosure, or destruction of, or damage to, Personal Data.

## Results

The study was initiated in July 2024, with the first participant’s first visit at the end of July 2024. As of June 2025, a total of 122 participants were recruited, and 74 completed visit 2 (3-month time point). The study is expected to be completed (the last participant’s last visit) by the first half of 2026. All data will be analyzed at the end of the study (after database lock, to maintain the double-blind nature of the study), followed by publications in peer-reviewed journals.

## Discussion

The Starter Liquid Infant Formula Trial (STARLIT) is among the first few clinical trials that will investigate the efficacy of the 2 HMOs, 2-fucosyllactose and lacto-N-neotetraose, on gut health, gut barrier integrity, and immune response, together with clinically relevant outcomes such as illness, infections, growth, and quality of life among Chinese infants born at term. *Bifidobacteria*, a key microbiome taxon during early life development, are often depleted in the gut of an infant receiving infant formula compared to breastfeeding [43]. One of the main drivers of this difference is the absence of HMOs in infant formula compared with breastmilk [44]. We therefore anticipate that consumption of an infant containing the 2 selected HMOs formula from birth to age 6 months will favor the growth of gut *Bifidobacteria* compared with the CG and should bring *Bifidobacteria* levels closer to those in the breastfeeding arm of the study. Given the central role of *Bifidobacteria* in gut microbiome maturation, we expect that other microbial taxa and functions may also be affected by the presence of the 2 HMOs and contribute to directing the gut microbiome maturation closer to the 1 observed in breastfed infants [45]. Finally, both *Bifidobacteria* and HMOs have been linked to multiple health outcomes [32]. With the breadth of end points collected in this study, we hope to be able to explore the importance of the addition of HMOs in early-life infant formula beyond the gut microbiome. Breastfeeding is the reference for infant nutrition as it is the best way to support optimal growth and development. Providing suitable solutions for infants that cannot be breastfed and that mimic breast milk composition as best as possible has become possible with ongoing research on breast milk composition as well as technological progress. To date, differences in health outcomes between breastfed and formula-fed infants remain, which may be attributed to the absence of key bioactive compounds such as HMOs in standard infant formulas [46,47]. HMOs are the third largest solid component in human milk, following lactose and lipids. They offer a wide range of functional benefits, including supporting immune and cognitive development [1,3,32,33,48]. These benefits may mostly be mediated by the impact of HMOs on the gut microbiome and its metabolic activity [49,50]. HMOs are nondigestible oligosaccharides that reach the lower part of the infant digestive track, where they can be used and transformed by the maturing gut microbiome. Specifically, they support the growth and metabolic activity of *Bifidobacteria* in early stages of life, which has been associated with multiple health benefits [51]. Technological and regulatory advancements now allow the inclusion of oligosaccharides identical to those found in human milk, such as 2-fucosyllactose and lacto-N-neotetraose, in infant formulas in China [32,33]. Hence, generating clinical evidence that supports the efficacy of these HMOs in this population is much warranted.

We hypothesize that the addition of 2-fucosyllactose and lacto-N-neotetraose to the infant formula will promote the growth of beneficial *Bifidobacteria* and drive the gut microbiome of infants closer to that of breastfed infants. Additionally, we propose that this bifidogenic effect may further benefit infant gut and immune health. Previous studies have shown that the fecal microbiome of most infants from China falls within a distinct enterotype from the rest of the world. More specifically, this enterotype found most predominantly in China is characterized by a relatively high abundance of *Proteobacteria* and more specifically of Enterobacteriaceae [52]. These taxa are considered opportunistic pathogens with their ability to alter the composition of the gut microbiome and favor gut dysbiosis [53,54]. They also have proinflammatory properties and have been associated with IBD pathogenesis and progression [55,56]. In contrast, among infants from the West, *Bifidobacterium* was found to be the dominant genus of the intestinal microbiota. Decline in *Bifidobacteria* and gut microbial dysbiosis has been linked to the increasing incidence of allergies and autoimmune diseases [57,58]. As mentioned earlier, in infants given formula supplemented with 2-fucosyllactose and lacto-N-neotetraose compared to control, there were significantly fewer reported incidences of bronchitis, respiratory tract infections, and use of antibiotics [27,30]. This observation has been linked not only to the bifidogenic effects of these HMOs but also to *Bifidobacterium*-related metabolic changes in the gut environment [28,29,59]. Hence, characterizing the role of HMOs in modulating the gut microbiome of Chinese infants and, in turn, assessing its impact on the immune health is central to this study [27-30,57-61].

Our study has several strengths. Its double-blinded design will ensure blinding of the participants, investigators, data collectors, outcome assessors, and data analysts to minimize bias in the reporting of the study outcomes. The study will be conducted across 5 different sites representing a wide geography within China and enabling a nonpreceded characterization of the effects of HMO supplementation in this population. Regarding the intervention products, the administration of a control formula identical to the test formula, apart from its HMO content, would allow us to clarify the efficacy of supplementation by 2-fucosyllactose and lacto-N-neotetraose with no further nutritional confounding factors. Yet, the 2 formulas must be precisely fully compliant with infant nutritional needs at this age. The nonrandomized BG will serve as a reference and help to gain insights into the contribution of these HMOs in shifting the gut microbiome and all other developmental outcomes closer to those of breastfed infants. The benefit of breastfeeding will be discussed with all parents who will meet a qualified lactation consultant before enrollment to ensure that they make an informed decision that is best for their infant. The service of a lactation consultant will be available over the course of the study to allow any parent to switch to breastfeeding at any time point.

The prospective and longitudinal nature of this study will allow us to collect detailed information on a comprehensive set of outcomes during the first year of life. Importantly, the fecal microbiome will be profiled using the most advanced and standard methodologies, such as NGS, in addition to quantitative polymerase chain reaction. This should enable us to shed light on the effects of HMOs on the dynamic maturation of the gut microbiome of Chinese infants at the taxonomic but also functional levels. HMO-mediated microbiome modulation of immune system development and fitness will be carefully monitored. We will capture infant illness weekly for 1 year using an IID, providing great granularity over AE occurrence. These IIDs will be used to generate an automated diagnosis that will be reviewed and confirmed by a study physician. Additionally, for the first time, we will use a novel Pediatric Immune System Index to assess immune competence that will allow the detailed characterization of gastrointestinal, upper respiratory tract infection, LRTI, and skin allergies by recording the duration, number of episodes, severity of health care visits, and treatment received. To complement this, fecal immune markers will also be quantified. Furthermore, we will be using validated questionnaires to capture details about gastrointestinal symptoms, sleep patterns, and quality of life to enhance our understanding of the effect of HMOs and their microbiome-modulating properties on infants’ well-being [27]. Importantly, we will also collect covariates, including maternal education, delivery mode, family history of allergy, infant dietary intake, and infant feeding (breastfeeding and formula feeding), medications, and treatments to adjust our analysis for potential confounding effects. In our study, the randomization is stratified by delivery mode. We hope to gain important insights into the effect of HMO supplementation, particularly among infants born by CS, in whom lower colonization rates of beneficial bacteria such as *Bifidobacterium* and *Bacteroides*, and higher colonization rates of *Clostridium*, *Lactobacillus*, *Enterobacter*, *Enterococcus*, and *Staphylococcus* have been reported [62]. This is particularly relevant considering the high rates of elective CS in China with an increase reported from 28.8% in 2008 to 36.7% in 2018 [63] and reaching up to 43.79% in 2019 according to the data published by the National Health Service and Quality Safety Report (obstetrics) in 2020 [64] This is far above the CS rates of 10%-15% of all deliveries suggested as reasonable by the WHO [65,66] and likely impacts the immune development of their infants, risk for allergy, atopy, and asthma, and intestinal gut microbiome diversity [67].

We acknowledge a few limitations in our study. While the study uses a comprehensive set of tools for assessing several outcomes, these may be perceived as burdensome to some subjects. Hence, the choice of not including systemic immune markers in addition to feces to reduce burden and risk linked to invasive procedures was made. Finally, generalization of results outside of China may be limited due to the geographical specificity of their gut microbiome.

In conclusion, this double-blind randomized controlled trial with a nonrandomized BG will be among the first studies in China to investigate the efficacy of a ready-to-feed infant formula containing 2-fucosyllactose and lacto-N-neotetraose in a matrix containing a unique whey protein concentrate coenriched in α-lactalbumin and MFGM on gut and immune health, as well as the effects on tolerance, growth, sleep, and quality of life. The much-anticipated results from this trial will strengthen the evidence base regarding the beneficial effects of HMOs in Chinese infants, as the study design should enable us to demonstrate that the addition of HMOs in infant formula contributes to supporting Bifidobacterium growth in the infant gut as well as the appropriate maturation of the gut microbiome and immune functions. This may help drive recommendations on target doses that are appropriate for observing beneficial changes in gut microbiome, gut maturation, gut barrier integrity, immune response, and other developmental outcomes.

